#### Direct-Acting Antiviral Therapy Initiation

DAAs were initiated by the study medical officer during visit 2/3 after reviewing and returning pretreatment assessment results to the participant. If the participant required a specialist review, DAAs were initiated (when appropriate) by the medical officer after the participant returned from the specialist review appointment.

#### On-Treatment Monitoring Visits

Participants commenced DAA therapy and received short on-treatment monitoring visits every 4 weeks (weeks 4, 8, and 12 for a 12-week course, plus weeks 16, 20, and 24 for a 24-week course). These visits include medication dispensing and questions about alcohol use, injecting drug use, medication adherence, and side effects. On-treatment visits are not required by the National Guidelines; they are included to collect study-related data.

#### Sustained Virologic Response 12 Assessment

After 12 weeks of treatment completion, the participants return to the clinic for the assessment of SVR12 using the Cepheid GeneXpert hepatitis C RNA test. If hepatitis C RNA is detected but <10 IU/mL, then the participant is retested in 12 weeks. If RNA is detected and within or above the quantitative range, the participant undergoes further testing using dried blood spot samples collected at screening and SVR12 to determine the next potential treatment course.

### Data Sources

#### Clinical Case Report Forms

Clinical data are collected in case report forms (CRFs) using the electronic database Open Medical Records System (OpenMRS); medical officers at the study site complete electronic CRFs (eCRFs) in OpenMRS first, but paper CRFs were used at the beginning of the study before eCRFs were finalized and are available if there are extended power outages or the database does not function properly. OpenMRS is an open-source medical records system; the database and the system are tailored to meet disease- and clinic-specific requirements. The OpenMRS database is run from a secure local server at each study site; backups of participant data are encrypted. Regular de-identified data exports are emailed to the data management team as a CSV (comma-separated values) file.

#### Visit 1/2 (Screening and Diagnosis): Case Report Forms 1 and 2

At visit 1/2 (Screening and Diagnosis), demographic data, drug use data, medical history, hepatitis C test results, and when participants received their diagnosis results were recorded.

Demographic data include age, sex, education level, employment status, income level, and residence locality. Drug use data include a history of injecting drug use, frequency of injecting, substances injected, receptive sharing of injecting equipment, history of and current methadone maintenance therapy, and alcohol consumption via the Alcohol Use Disorders Identification Test – Consumption (AUDIT-C) questionnaire.

#### Visit 2/3 (Baseline): Case Report Form 3 and Visit 3 /4 (Specialist Review) Case Report Form 7

At visit 2/3 (Baseline), pretreatment assessment laboratory results, clinical review, and treatment plan were recorded in eCRFs. A specialist review is captured in an eCRF by the medical officer when the participant returns to the study site, including laboratory investigation results, examination notes, and the recommended treatment plan.

#### On-Treatment Monitoring—Case Report Form 4

At monitoring visits (on treatment, end of treatment), the following data are collected: alcohol use in the past month using the adapted AUDIT-C questionnaire, injecting drug use in the past month (including frequency of injecting, substance/s most commonly injected), receptive sharing of injecting drug use equipment, current methadone maintenance therapy, side effects experienced, medication adherence (any missed doses, how many missed doses, and whether the doses were missed on consecutive days), and any new medications.

#### Sustained Virologic Response 12 Weeks Post-Treatment Completion Assessment: Case Report Form 5

At SVR12 visit (12 weeks after treatment completion), the following data are collected: alcohol use via the AUDIT-C questionnaire, injecting drug use in the past month (including frequency and substance), receptive sharing of injecting drug use equipment, current methadone maintenance therapy, hepatitis C RNA test result (SVR12 assessment), and details on when the participant received the result (on the same day or the next appointment).

#### Study Discontinuation: Case Report Form 6

When a participant exits the study, the date of exit and the reason for discontinuation (ineligible, loss to follow-up, participant decision, etc) are recorded. Participants are contacted at least three times over 4 weeks by phone and via their secondary contact at least once. A peer worker from the Burnet clinic also tries to contact the participant via outreach work. If there is no response or the participant is incarcerated, they are classified as lost to follow-up; if the participant has withdrawn from the study, this decision and the reason are recorded.

#### Participant-Completed Questionnaires

Participant-completed questionnaire data are collected in Research Electronic Data Capture (REDCap) [25]. REDCap is a web-based database system that hosts customized project-specific questionnaires. All participants completed a behavioral questionnaire at the first study visit (Screening visit). It collects data on demographics, lifetime health care utilization (locations and providers), alcohol use, injecting drug use, incarceration history, sexual behaviors, experiences of stigma/discrimination, and reason for seeking a hepatitis C test.

All participants also complete an acceptability survey at the Screening/Diagnosis visit, after receiving the results of anti-hepatitis C Ab and/or hepatitis C RNA tests. It collects information on referral to the clinic, how they found out about the clinic, how they got to the clinic (including transport mode, time spent, and cost), level of comfort in talking with a health provider about risk behaviors, confidence in the knowledge of hepatitis C, hepatitis C knowledge, acceptability of the Ab rapid diagnostic test (including the collection of blood samples, trust in test accuracy, and wait to receive results), and acceptability of POC GeneXpert hepatitis C RNA test (including the collection of blood samples, trust in test accuracy, and wait to receive results) using a 5-point Likert scale for acceptability and confidence, and testing preferences by asking which test option participants would choose.

Participants complete a combined behavioral and acceptability survey at the SVR12 visit. The survey collects data on the past months’ health care utilization, alcohol use (modified AUDIT-C questions for the past month), injecting drug use, acceptability of the testing and treatment process, details of how often participants attended the clinic, any costs to the participant, confidence in the knowledge of ongoing liver-related care required, and how to prevent reinfection.

#### Participant Interviews

Semistructured interviews will be conducted with 10 to 15 participants from each study site. The interview guide includes questions related to the experiences and views participants have toward services at the clinic, POC hepatitis C testing (both Ab and RNA testing), and treatment course. These data complement the acceptability survey data.

#### Provider Interviews, Surveys, and Clinical Workflow Observations

Semistructured interviews will be conducted with providers from each study site. Provider interviews will ask about the processes involved in conducting the tests, the processes involved in providing treatment, the referral process, and the processes for following up participants. These data will contribute to assessing the feasibility of the model of care from the provider perspective, contributing to domains of practicality and implementation. The provider survey will be completed by providers at each study site and will cover the acceptability and usability of Ab and RNA test devices and procedures. Clinical workflow observations recording workflow and time taken by staff members to complete specific aspects of workflow were completed midway through the study. These workflow observations will contribute to intervention complexity assessments.

#### Document Review

A document review of the GeneXpert device requirements, DAA requirements, training requirements, project meeting minutes, and monitoring visit reports will be used to inform intervention complexity assessments and practicality and implementation feasibility domains. GeneXpert device error reports and maintenance reports will also be included in the feasibility and intervention complexity assessment.

### Data Management

All quantitative CRF and survey data are managed in Stata SE 15 (Stata Statistical Software: Release 15, StataCorp LLC). OpenMRS and REDCap CSV file exports are imported into Stata and labeled and cleaned before conducting data quality checks and analysis. Regular data quality checks (every 2-4 weeks) and subsequent timely query resolution (<14 days) are performed to ensure quality assurance by the Burnet Institute project staff. The list of study IDs from the enrollment log is compared with OpenMRS and REDCap exports to ensure that no records are missing. Key data, including visit dates, test dates, test results, DAA therapy regimen and commencement date, and study discontinuation information, are checked for completion and logical responses.

Interviews will be audio recorded, transcribed, and translated into English. Transcript data will be managed using NVivo (QSR International).

### Statistical Analysis

#### Primary Outcomes

Outcomes 1-4 measuring the proportion of uptake across the cascade of care will be used to assess the feasibility of the model of care in terms of demand and practicality.

##### Outcome 1: The Proportion of Anti-Hepatitis C Antibody-Positive Participants who Received a GeneXpert Hepatitis C RNA Polymerase Chain Reaction Test

Descriptive statistics of the number and proportion of anti-hepatitis C antibody-positive participants who receive a GeneXpert hepatitis C RNA PCR test are provided. Any difference between sites will be determined using chi-square tests.

##### Outcome 2: The Proportion of Hepatitis C RNA Polymerase Chain Reaction-Positive Participants who Are Initiated on Direct-Acting Antiviral Therapy

Descriptive statistics of the number and proportion of hepatitis C RNA PCR-positive participants who are initiated on DAAs are provided. Any difference between sites will be determined using chi-square tests.

##### Outcome 3: The Proportion of Participants Initiated on Treatment who Complete Therapy

Descriptive statistics of the number and proportion of participants initiated on treatment who complete the therapy (defined as picking up the last 28-day bottle of medication and reporting ≤7 days missed doses) are provided. Any difference between sites will be determined using chi-square tests.

##### Outcome 4: The Proportion of Participants who Completed Treatment who Achieve Sustained Virologic Response 12

SVR12 is defined a priori as an undetectable hepatitis C RNA viral load using hepatitis C RNA PCR testing on the GeneXpert platform at least 12 weeks after therapy completion. Intention-to-treat SVR is defined by undetectable HCV RNA among all participants initiating treatment. Modified intention-to-treat SVR is calculated for participants who initiated treatment and have SVR data available (ie, the SVR test was performed, and the results are available).

Care cascade outcomes (primary outcomes 1-4) describe the proportion who have completed diagnosis, pretreatment assessments, and initiation of DAA therapy; completed DAA therapy; and achieved SVR12. These care cascade outcomes will be descriptively compared with historical outcomes to give context to these results in the study results paper.

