#### Study Sites

The study is being conducted at 2 community clinics in Yangon: the Burnet Institute Thingangyun Key Population Service Clinic (hereafter referred to as the Burnet clinic) and the Myanmar Liver Foundation (MLF) Than Sitt Charity Clinic (hereafter referred to as the MLF clinic). Clinics are staffed by a trained GP (study medical officer), a nurse, and a laboratory technician for the duration of the study, plus a peer worker at the Burnet clinic and reception staff at MLF clinic. These study sites are separate from the hospital program sites described earlier.

The Burnet clinic provides health care services primarily to PWID, including needle and syringe distribution. The Burnet clinic is located in the Thingangyun township near the major methadone treatment center in central Yangon.

The MLF clinic serves the general population of patients with liver disease, with a focus on hepatitis B and hepatitis C care. MLF is well known across Myanmar for providing hepatitis B vaccination and treatment and hepatitis C testing and treatment; it runs several clinics across the country. MLF clinics provide outreach hepatitis C screening to various townships on an ad hoc basis, with those who test positive referred to MLF clinics for further testing and, if available, treatment through research studies, philanthropic projects, and other cost-sharing arrangements. The MLF clinic in Yangon also advertises its services via Facebook and accepts referrals from physicians for patients with elevated liver enzymes and other indicators of hepatitis B or hepatitis C.

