#### Recruitment

Recruitment into the study was based on prescreening eligibility assessment (criteria described further in *Study Assessments, Pretreatment Assessments* section). At the Burnet clinic, the study was advertised to potential participants using flyers displayed at the methadone treatment centers in Yangon and through Burnet peer outreach workers distributing flyers and speaking with PWID about the study. Burnet peer outreach workers also assessed potential participants for eligibility for enrollment in the study and made initial screening appointments with the nurse and medical officer at the clinic.

MLF clinic medical officers registered potential participants (including those previously screened anti-hepatitis C Ab positive) before commencement of the study and then invited them to attend the clinic in order of registration date. Patients attending the clinic on specified recruitment days (3 to 5 days per week) were also offered participation in the study.

At the initial study visit, the study nurse explained the purpose and procedure of the study to interested participants. Pre-enrollment eligibility was then assessed by the study nurse, and the consent procedure was conducted by the study nurse and medical officer.

Study recruitment commenced at the MLF clinic on January 30, 2019, and at the Burnet clinic on February 4, 2019; the last participant was recruited on September 30, 2019. Each clinic aimed to start 225 participants on DAA therapy; a total of 585 3-month treatment courses were available for the study, including some 6-month courses allocated to treat cirrhotic participants.

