#### Direct-Acting Antiviral Therapy

Participants who tested RNA detected (or positive) in the study could then receive a combination DAA therapy of sofosbuvir (400 mg) and daclatasvir (60 mg). Those with an aspartate aminotransferase to platelet ratio index (APRI) <2.0 (noncirrhotic) were offered a 12-week course. Those with an APRI ≥ 2.0 (cirrhotic) were offered a 24-week course, consistent with the national Simplified Treatment Guidelines for Hepatitis C Infection. A previous APRI validation study found that an APRI <2.0 reliably excluded cirrhosis in 85% of patients, with a negative predictive value of 91% [24]. (In line with the updated National Guidelines [second edition, July 18, 2019], the APRI cutoff was changed to 1.5 from August 6, 2019.)

All participants were reviewed and initiated on therapy by the study medical officer (a trained GP) at the study site. A specialist review was only required for those with signs of liver decompensation; the study medical officer referred to a consulting hepatologist as necessary and to other specialists at the local tertiary hospital at his or her discretion for other major comorbidities. A total of 4 weeks of medication is dispensed at the study site by the medical officer or nurse (site dependent) at baseline, week 4, and week 8 of treatment and at weeks 12, 16, and 20 for those on a 24-week course. Participants self-administer the combination therapy daily; adherence is monitored using self-report and pill counting if the participants return medication bottles.

The exclusion criteria for commencing DAA therapy in the study included (1) no active hepatitis C infection, (2) HIV co-infection, (3) hepatitis B virus co-infection, (4) active tuberculosis/on tuberculosis treatment, (5) eGFR <30 mL/min/1.73m^2^, (6) pregnancy, and (7) taking medications with serious drug-drug interactions with sofosbuvir/daclatasvir, which that participant is unable/unwilling to cease.

Participants with decompensated cirrhosis are eligible to access therapy through the study under the supervision of a consultant hepatologist if recommended after a consultant review. Consultant hepatologists are available on the weekends at the MLF clinic to see participants from the Burnet and MLF clinics; participants must attend the MLF clinic or Yangon Specialty Hospital to complete a specialist review. Advice from the consultant hepatologist is available via phone call and, if required, at other times.

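### Outcome 3 pools 12- and 24-week courses and compares clinics by a crude chi-square, so if the 24-week share differs by clinic, part of any site difference reflects course length

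*Protocol article*

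**What the plan says.** The protocol article, under Outcome 3 in Statistical Analysis, reports the "number and proportion of participants initiated on treatment who complete the therapy". Completion is defined the same way for everyone: "picking up the last 28-day bottle of medication and reporting ≤7 days missed doses". For the site comparison it states: "Any difference between sites will be determined using chi-square tests". That section mentions neither a split nor a stratification by course length.

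The section Direct-Acting Antiviral Therapy sets two course lengths by APRI. "Those with an aspartate aminotransferase to platelet ratio index (APRI) <2.0 (noncirrhotic) were offered a 12-week course", and those at or above the cutoff were offered 24 weeks. The cutoff was lowered to 1.5 from August 6, 2019, while recruitment was still open. Four-week supplies are dispensed "at baseline, week 4, and week 8 of treatment and at weeks 12, 16, and 20 for those on a 24-week course".

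Under Study Sites, the Burnet clinic mainly serves people who inject drugs. Of the other clinic the article says: "The MLF clinic serves the general population of patients with liver disease". Under Recruitment, each clinic aimed for 225 starts, and "a total of 585 3-month treatment courses were available for the study, including some 6-month courses allocated to treat cirrhotic participants".

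**The concern.** The completion rule requires the last bottle to be collected, and the last bottle comes after a different number of return visits on the two courses. If people at both clinics are equally likely to return for each pick-up, completion is still lower on the longer course. Course length therefore predicts the outcome by construction.

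If course length is also unevenly spread over the clinics, the crude comparison mixes two things: how well each clinic keeps people in care, and how many of its patients were assigned the longer course. The clinic with more 24-week courses would look worse at equal retention. In the other direction, poorer retention at the clinic with fewer 24-week courses could be hidden. Outcomes 1 to 4 are used to judge the feasibility of the model, so a site difference in completion would naturally be read as a difference in retention.

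**Working it through.** The article gives no sample-size calculation, significance level or expected completion rate for this comparison, so there is no stated figure to reproduce. Its targets agree with each other: 2 × 225 = 450.

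**Inputs from the article**
- Return pick-ups after baseline: weeks 4 and 8 (two) on the 12-week course; weeks 4, 8, 12, 16 and 20 (five) on the 24-week course.
- 225 starts per clinic.
- Stock: 585 three-month courses for 450 starts leaves 585 − 450 = 135. If every spare course extends one participant to 24 weeks, the overall 24-week share is at most 135/450 = 30%.

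**Assumptions (not in the article)**
- One return probability r per pick-up, the same at every visit, on both courses and at both clinics; r = 0.99, 0.97 or 0.95.
- No failures from missed doses.
- 24-week shares by clinic of 20%/10%, 40%/20% and 50%/10%. The last two both average 30% and so use the whole stock ceiling; 50%/10% is an extreme split.
- A two-sided 5% test.

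**Step 1. Completion by course: r² for 12 weeks, r⁵ for 24 weeks**

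| r | 12 weeks | 24 weeks | Gap |
|---|---|---|---|
| 0.99 | 0.9801 | 0.9510 | 0.0291 |
| 0.97 | 0.9409 | 0.8587 | 0.0822 |
| 0.95 | 0.9025 | 0.7738 | 0.1287 |

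**Step 2. Site difference from mix alone.** Completion at a clinic with 24-week share f is (1 − f)r² + f·r⁵, so the difference is (f₁ − f₂)(r² − r⁵). At r = 0.97 and 40%/20%: 0.20 × 0.0822 = 0.0164, or 1.6 points (90.8% against 92.4%).

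**Step 3. Chance that the crude test gives p < 0.05.** With difference d, mean completion p̄, null standard error s₀ = √(2p̄(1 − p̄)/225) and actual standard error s₁ = √([p₁(1 − p₁) + p₂(1 − p₂)]/225), the chance is Φ((d − 1.96s₀)/s₁) + Φ((−d − 1.96s₀)/s₁). At r = 0.97 and 40%/20%, s₀ and s₁ are both 0.0261, giving 0.092 + 0.005 = 9.6%.

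| 24-week shares | r = 0.99 | r = 0.97 | r = 0.95 |
|---|---|---|---|
| 20%/10% | 0.3 points; 5.5% | 0.8 points; 6.3% | 1.3 points; 7.1% |
| 40%/20% | 0.6 points; 6.6% | 1.6 points; 9.6% | 2.6 points; 12.5% |
| 50%/10% | 1.2 points; 11.5% | 3.3 points; 24.2% | 5.1 points; 35.6% |

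**Step 4. Does stratifying remove it?** In 20,000 simulated trials per scenario with no site effect within either course length, the Cochran-Mantel-Haenszel test stratified by course length rejected close to 5% of the time. At 50%/10% it rejected in 5.1% (r = 0.97) and 4.9% (r = 0.95), where the crude chi-square rejected in 24.0% and 36.0%.

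The fixed seven-day allowance is left out of these figures. It is 7/84 = 8.3% of a 12-week course and 7/168 = 4.2% of a 24-week course, so it acts in the same direction.

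**The case against.** The strongest reply has four parts.

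- **Detail left to fuller documents.** The article condenses a fuller protocol, and a split by regimen is typical of an analysis plan. That is fair for anything the article leaves open, and a split may well exist there. But the article names the between-site test, and that test is crude.
- **The comparison is descriptive.** The article sets no decision rule on it and does not attribute a difference to clinic performance. This stands. If the two cohorts complete at different rates, the chi-square validly tests that. The rejection rates above are error rates only for the null hypothesis of equal completion within each course length.
- **The pooled figure is legitimate.** Treating people for 24 weeks at a community clinic is part of the model under study, and five return visits are part of its burden. This also stands. A reader might infer that the pooled proportion is invalid; it is not.
- **The difference in mix is not shown.** No section gives the 24-week share by clinic. A reader might infer that the liver clinic must have more 24-week courses, or that a site difference would be nothing but a different cirrhosis mix. The article supports neither. It makes a different mix plausible and leaves its size and direction unknown. With equal mixes and equal retention the artefact is zero.

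Stratifying on course length also leaves population and recruitment route different between sites, so a stratified result would not isolate clinic performance.

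**Conclusion.** The point holds in a limited form and is a cheap improvement rather than a defect that invalidates the outcome. The two-against-five difference in pick-ups follows directly from the schedule; a difference in mix between clinics is an assumption.

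With modest differences in mix or high retention, the artefact is a point or two and the crude test is only mildly affected. It becomes material only when both the mix differs strongly and returns are lost at a noticeable rate. The pooled proportion and the crude test remain sound as descriptions of the two cohorts. What they cannot support alone is a statement that one clinic retains people better than the other, or that the two retain them equally well.

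**What to change.** In the analysis text for outcome 3:

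1. Keep the pooled proportion and the crude site comparison as the description of the treated cohorts.
2. Report completion separately for 12- and 24-week courses, overall and by site.
3. Add a site comparison stratified by assigned course length, as a Mantel-Haenszel risk difference with 95% CI, and base any statement about retention differing between clinics on it.
4. State that differences in population and recruitment route between the clinics remain.

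This takes a few sentences and should need no new data: Data Management already lists "DAA therapy regimen and commencement date" among the key items checked. The price is a wide interval in the smaller 24-week stratum. The change concerns analysis and reporting only and implies nothing about course length or the APRI cutoff.
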